For the intra- and intercluster correlation (ICC), literature indicates a moderate ICC of 0.059 for antibiotic prescription behavior [35,36]. This estimate seems appropriate as moderate differences in antibiotic prescription behavior are expected within and between different physicians at participating sites, which mostly follow the IGGI guidelines, however, with some internal adjustments. Indeed, the most recent point prevalence survey of antimicrobial use and health care–associated infections in Belgian acute care hospitals (results of the global point prevalence survey and European Center for Disease Prevention and Control point prevalence survey) reports 77% compliance with IGGI guidelines [37]. Additionally, 3 participating sites are part of the same Hospital Outbreak Support Team network, that is, Heilig Hartziekenhuis Mol, AZ Turnhout, and AZ Herentals in the Hospital Outbreak Support Team Network Kempen, which has the specific goal to align antimicrobial stewardship. All centers use the same EPR (CWS). The major difference would be expected between UZ Leuven, as an academic hospital, and the other participating sites, as regional hospitals. The AFC is currently only available in the CWS EPR system, and therefore, we were unable to include other academic centers as well. A sensitivity analysis of academic vs regional hospitals will be performed.

Considering the number of hospitalizations per year in each center and a prevalence of 6% of BLALs [8], we expect an inclusion rate of 3285 participants.

Sample size and power calculations were carried out according to the methods described by Hemming et al [38], using the Shiny CRT Calculator [39]. Based on the design given in Figure 1, assuming a discrete time decay (allowing correlations between periods to decay with each period), a within-period ICC of 0.059 and an autocorrelation (ratio of between-period and within-period ICC) of 0.6, this study will have 80% power to detect a statistically significant difference between control and intervention using a 2-sided significance level of 5%, assuming 4.6% and 9.9% of patients to have the primary end point in the control and intervention group, respectively. This sample size calculation is based on patient-level appropriate prescribing proportions and is considered a conservative approximation for the cumulative window-based primary end point.

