### Statistical Analysis

The primary endpoint is cumulative guideline-concordant use of first-line and/or narrow-spectrum beta-lactam antibiotics according to IGGI-based local guidelines, assessed across predefined assessment windows up to day 100 (days 1, 30, and 100). Within each window, guideline concordance is scored at the patient level in an any or ever manner as 1 if at least one in-hospital systemic antibiotic course is guideline-concordant and 0 if otherwise. If multiple courses occur within a window, the window is considered concordant if any course meets guideline criteria. This any or ever approach was chosen in line with the quality-improvement objective of the AFC intervention, capturing whether appropriate first-line therapy was achieved within a care window while limiting instability due to multiple within-episode treatment changes. Windows without in-hospital systemic antibiotic administration are considered not applicable (“no opportunity”) and are excluded from the denominator.

For each patient, a cumulative weighted guideline-concordance score is calculated at day 100 as the proportion of applicable windows with guideline-concordant therapy (*sᵢ/nᵢ*). The primary comparison between intervention (AFC) and control will use a binomial generalized linear mixed-effects model with logit link, modeling *sᵢ* out of *nᵢ*, including fixed effects for study phase and period, and a random intercept for hospital to account for clustering in the crossover design. A prespecified adjusted model will additionally include age, sex, and the Charlson comorbidity index. Patients without any applicable windows will be excluded from this analysis and reported separately. The primary estimand targets the period during which the AFC is expected to plausibly influence prescribing through contemporaneous decision support and short-term label adjustment.

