Sensitivity analyses will include evaluation of alternative covariance structures for within-cluster and within-period correlation (eg, exchangeable or autoregressive), with model selection guided by goodness-of-fit criteria, and estimation using generalized estimating equations with robust SEs to obtain marginal effect estimates and assess robustness to modeling assumptions. As a robustness check, we will report the proportion of patients with any recorded in-hospital follow-up within the shared EPR network (CWS) by study phase and period.

A detailed statistical analysis plan and data management plan will be finalized before database lock.

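### The primary model's lone hospital random intercept leaves out the between-period decay assumed in the sample size, so its standard error is too small and, on the protocol's own inputs, its 5% test runs at about 9–15%

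*Protocol article*

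**What the plan says.** All places are in the Methods of the protocol article.

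- **Sample Size Determination.** Power is computed "assuming a discrete time decay (allowing correlations between periods to decay with each period"), with "a within-period ICC of 0.059 and an autocorrelation (ratio of between-period and within-period ICC) of 0.6". The claim is that "this study will have 80% power to detect a statistically significant difference between control and intervention", "assuming 4.6% and 9.9% of patients to have the primary end point in the control and intervention group, respectively", at a two-sided 5% level. On numbers: "we expect an inclusion rate of 3285 participants".
- **Statistical Analysis, primary comparison.** The binomial model is specified as "including fixed effects for study phase and period, and a random intercept for hospital to account for clustering in the crossover design". The prespecified adjusted version adds age, sex and the Charlson index, but no further random effect.
- **Statistical Analysis, sensitivity analyses.** Exchangeable and autoregressive structures will be compared by goodness of fit, together with "estimation using generalized estimating equations with robust SEs to obtain marginal effect estimates". Both are labelled sensitivity analyses.
- **Design.** Allocation is by hospital, in 3-week periods, with four sequences. In each sequence the intervention and control periods are two periods apart. Figure 1, which would show how often the sequence is run, is not available here.

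**The concern.** The two sections describe different data. A hospital intercept alone sets the ratio of between-period to within-period correlation to 1; the sample size sets it to 0.6 per period step, falling further with distance. The fixed period effects do not close the gap, because they remove only calendar variation common to all hospitals and not a hospital's own fluctuation from one period to the next.

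Phase is constant within a hospital-period, so that fluctuation goes straight into the AFC-versus-control contrast. The primary model treats patients as independent once hospital, period and phase are accounted for. If the fluctuation exists to the degree the sponsor assumed, the standard error is too small, the interval too narrow and the p-value too low. This is the trial's headline test, in an open-label, non-randomized design with few clusters. An AFC benefit could be declared on ordinary hospital-period noise.

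**Working it through.** **Inputs.** Total 3285; about 30% receive antibiotics and so enter the primary analysis (3285 × 0.30 ≈ 985); 9 hospitals; ICC ρ = 0.059; autocorrelation 0.6; rates 4.6% and 9.9% overall. The control rate among treated patients is about 15.5% (10.5% + 5%; compare 4.6%/0.30 = 15.3%). Intervention and control are two periods apart, so their correlation ratio is 0.6² = 0.36. The number of passes k through the four-period sequence is an assumption: a pass takes 12 weeks and recruitment is planned for 11 months (about 48 weeks), so k = 1 to 4.

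**1. The stated 80% power.** I used generalized least squares on hospital-period means with fixed period effects. The covariance is s²[ρ·0.6^lag], plus s²(1−ρ)/m on the diagonal, where s² = (0.046×0.954 + 0.099×0.901)/2 = 0.0665 and m = 3285/(18k).

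- k = 1: SE 0.0255; 0.053/0.0255 = 2.08; power Φ(2.08 − 1.96) ≈ 55%.
- k = 2: SE 0.0179; 0.053/0.0179 = 2.96; power ≈ 84%, or 80.1% with a t reference on 36 − 8 − 8 − 1 = 19 df.
- k = 3 and 4: about 94% and 97%.

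The stated 80% is therefore reachable with two passes. One pass falls well short. Without Figure 1 the value cannot be pinned down uniquely.

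**2. Closed form for the primary test.** For one within-hospital contrast, true variance over model variance is 1 + mρ(1 − 0.36)/(1 − ρ), with m = 985.5/(18k). The rejection rate under no effect is 2[1 − Φ(1.96/√ratio)].

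- k = 1, m = 54.75: ratio 1 + 54.75×0.059×0.64/0.941 = 3.20; √3.20 = 1.79; rejection rate 27%.
- k = 2, 3, 4: ratios 2.10, 1.73, 1.55; rates 18%, 14%, 11.5%.

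This treats each intervention–control pair in isolation. With several passes, neighbouring contrasts partly cancel. The full matrix version (true covariance under the intercept-only estimator) gives the slightly lower rates in the table.

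**3. Simulation of the stated model.** I used logit-normal hospital-period effects calibrated to ICC 0.059 with correlation 0.6^lag and no AFC effect, and fitted period, phase and a random hospital intercept with a Wald z-test (3000 runs each).

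| Passes | Patients per hospital-period | Mean model SE (log OR) | True SD | Rejections, simulated | Rejections, matrix form |
|---|---|---|---|---|---|
| 1 | 55 | 0.187 | 0.325 | 25.5% | 26% |
| 2 | 27 | 0.186 | 0.254 | 14.9% | 15.5% |
| 3 | 18 | 0.185 | 0.235 | 12.2% | 11.5% |
| 4 | 14 | 0.181 | 0.215 | 9.7% | 9.6% |

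With autocorrelation set to 1 the same model rejected 4.5% of the time, so the excess comes from the omitted hospital-by-period variance.

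**4. Milder or different inputs.**

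- Matrix form, two / four passes: autocorrelation 0.9 gives 8.4% / 6.4%; ICC 0.03 gives 10.4% / 7.3%; ICC 0.01 gives 6.7% / 5.8%. Simulations at two passes gave 7%, 11% and 6%.
- A constant between-period ratio of 0.6 without further decay gives 14%, 10.5% and 8.5% for two, three and four passes.
- One site holding half the patients gives 15% (two passes) and 10% (four).

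**5. Does the remedy work?** Adding a random hospital-by-period effect (500 runs each) gave 14.4%, 8.8% and 7.0% with a z-test for one, two and four passes, and 5.8%, 7.0% and 6.2% with t degrees of freedom based on hospital-periods. The extra effect alone is not enough with 9 hospitals.

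**The case against.** **The inflation is conditional.** The ICC is a literature value for prescribing behaviour in general, not for guideline concordance in labelled, antibiotic-treated patients, and no separate source is given for the autocorrelation. If the true decay is slight or the ICC small, the test is only mildly liberal. This stands, and it is why the size is given as a range.

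**The single-pass figure.** A reader might infer that the test rejects a true null 25% of the time. The documents do not support that as the expected case: one pass gives about 55% power against the stated 80%, and 11 months leaves room for more than one 12-week pass, although Figure 1 could show staggered hospitals.

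**Larger figures.** Analysing all 3285 patients would push the single-pass rate to about 45%. That is not the planned analysis, because patients without an applicable window are excluded.

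**The plan already considers other structures.** It does, and an autoregressive fit would probably expose a discrepancy. The arm-masked review also estimates the between-period correlation, but it serves decisions on recruitment, periods and centers. Neither step changes the model that yields the primary p-value.

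**Small-sample detail belongs in the SAP.** This also stands. The article's silence on degrees of freedom is not an error, and nothing says that the robust GEE standard errors will be uncorrected. The finding is the random-effects structure, which the article states explicitly.

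**Conclusion.** The point holds. The primary model and the sample size assume incompatible correlation structures, and the primary model's choice makes the standard error of the AFC effect too small. Under the protocol's own ICC and autocorrelation, the nominal 5% test rejects a true null about 9–15% of the time for two to four passes. With autocorrelation 0.9, or ICC 0.01–0.03, it is about 6–10%.

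The figures assume that the ICC of 0.059 carries over to the treated subset, that the 9 hospitals are of near-equal size, and that the number of passes lies in the range shown. They count one window per patient. Correlation among a patient's up to three windows was not simulated; since the model has no patient-level effect, it could only add to the inflation. The direction is certain whenever hospital-by-period variance exists. The exact size is not known from the documents.

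**What to change.** Make the primary model fixed phase and period, a random hospital intercept, and a random hospital-by-period effect, or replace the latter with the discrete-time decay structure used for the sample size. Test phase with small-sample degrees of freedom (Satterthwaite or Kenward-Roger type), or with a t-test on hospital-period summaries. Both parts are needed, since the extra effect with a z-test still left about 7–14%. Keep the intercept-only model as a sensitivity analysis.

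As a suggestion for the SAP, give the GEE analysis a small-sample correction (for example Kauermann-Carroll or Mancl-DeRouen) with t critical values.

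The cost is a change of wording and model code before database lock, which is planned for late 2026. Confidence intervals will be wider. No new data are required.

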Allocation is performed on the hospital level (participating sites) before the start of this study to prevent contamination of effect between the intervention and control phases (ie, so that physicians will not receive information through the AFC while having to use conventional means for different patients at the same time). The allocation is nonrandomized and operationally predefined based on the availability of a single trained research team responsible for on-site implementation across hospitals. Inclusion periods are sufficiently long and distributed over calendar time to account for seasonal variation. A crossover cluster-controlled design was used to reduce potential confounding related to temporal and organizational factors in clinical practice, such as variation in staffing and workload among treating physicians. Residual temporal and cluster-level confounding will be further addressed in the statistical analysis by including study period and hospital as model terms.

During separate intervention phases, hospital physicians will receive the intervention, that is, BLAL CDS. Each of the crossover periods will be 3 weeks long. However, a washout period of 3 weeks is also taken into account to allow the patient population to be sufficiently “new” before the cluster transitions to the next condition. We will use the sequences I-x-C-x, x-I-x-C, C-x-I-x, and x-C-x-I (where I=intervention, ie, use of the AFC, and C=control, ie, standard of care [SOC], no use of the AFC, and x=washout period), and each cluster will be allocated to one of these sequences (Figure 1). Information about the assigned sequence is available to all people and groups involved in the research (ie, unblinded, open study).

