### Baseline Measurements

For each patient, baseline data will be recorded in the electronic case report form using the REDCap (cf. Infra). The collected information will encompass sociodemographic details, clinical data, and specific information on the BLALs as registered in the EPR. Sociodemographic information will include age, gender, and contact details of both the general physician and the community pharmacist. Clinical information will capture the reason for admission and, if applicable, the condition requiring antibiotic treatment, categorized according to the *ICD* (*International Classification of Diseases*) codes. Additionally, any antibiotics (Anatomical Therapeutic Chemical codes J) already administered during the current hospitalization will be documented. To assess comorbidity burden, the presence of specific conditions contributing to the Charlson Comorbidity Index will be recorded, including myocardial infarction, congestive heart failure, peripheral vascular disease, cerebrovascular disease, dementia, chronic pulmonary disease, rheumatologic disease, peptic ulcer disease, liver disease, diabetes, hemiplegia or paraplegia, renal disease, malignancy (localized or metastatic), leukemia, lymphoma, and acquired immunodeficiency syndrome. Information on BLALs will be extracted from the allergy registration module within the EPR. This will include the registration date of the BLAL, the specific drug involved (Anatomical Therapeutic Chemical code), the onset date of the allergic reaction, reported symptoms, and the source of information. Additionally, the probability of label accuracy, as indicated by the reporter, will be documented.

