Secondary endpoints include guideline-concordant beta-lactam use at each individual assessment window (including day 200), delabeling or refinement rate, beta-lactam tolerance, antibiotic switching, ICU admission, readmission, resistant organism outcomes, LOS, mortality, and cost outcomes. Outcomes at day 200 are analyzed as secondary durability measures, as longer-term prescribing may be influenced by label reappearance or documentation changes unrelated to the index intervention. Secondary endpoints will be analyzed using hierarchical mixed-effects models appropriate to outcome type (binary, continuous, or time-to-event), with fixed effects for study phase and period and clustering by hospital. Process evaluation outcomes will be analyzed descriptively.

Predefined subgroup analyses will assess potential effect modification by including phase-by-subgroup interaction terms in the primary model. Subgroups of interest are BLAL type (penicillin vs other labels), reported reaction severity category, time since label registration, infection type (prophylaxis vs therapeutic indication), ICU admission status, and hospital type (academic vs regional). Subgroup analyses will focus on the primary endpoint and are considered exploratory and hypothesis-generating. 

Moreover, because the AFC is expected to influence prescribing primarily through label delabeling or refinement, we will perform an exploratory implementation analysis within the AFC phase. Patients will be classified as with implementation if the BLAL was delabeled or refined after the AFC recommendation, and as not with implementation if otherwise. The cumulative primary endpoint (*sᵢ/nᵢ* up to day 100) will be summarized by implementation status; any between-group comparisons will be considered descriptive and interpreted cautiously, as implementation is a postallocation process measure and may be confounded.

No formal adjustment for multiplicity will be applied. Secondary and subgroup analyses will be interpreted with caution.

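### Allocation is nonrandomized and phases contain different patients, yet the prespecified adjusted model omits label type, reaction severity and time since label registration

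*Protocol article*

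**What the plan says.** All references are to the Protocol article.

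- **Allocation (Design).** "The allocation is nonrandomized and operationally predefined based on the availability of a single trained research team". Confounding is to be handled as follows: "Residual temporal and cluster-level confounding will be further addressed in the statistical analysis by including study period and hospital as model terms".
- **Primary model (Statistical Analysis).** A binomial mixed model for concordant windows out of applicable windows, "including fixed effects for study phase and period, and a random intercept for hospital to account for clustering in the crossover design". It has no patient-level covariate.
- **Adjusted model (Statistical Analysis).** "A prespecified adjusted model will additionally include age, sex, and the Charlson comorbidity index". The article does not say that this model carries the primary inference.
- **Data collected (Baseline Measurements).** The label's registration date and "the specific drug involved (Anatomical Therapeutic Chemical code), the onset date of the allergic reaction, reported symptoms, and the source of information". Also, "any antibiotics (Anatomical Therapeutic Chemical codes J) already administered during the current hospitalization will be documented".
- **Subgroups (Statistical Analysis).** "Subgroups of interest are BLAL type (penicillin vs other labels), reported reaction severity category, time since label registration", followed by infection type, ICU status and hospital type. They enter as exploratory phase-by-subgroup interactions.
- **Limitations (Discussion).** The article concedes that some residual confounding from the nonrandomized allocation cannot be ruled out.

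**The concern.** In this crossover each hospital is its own control, but each patient is not. Anyone already enrolled is excluded, so a hospital's intervention and control phases contain different people. If the mix of labels differs between two 3-week phases of the same hospital, neither the period term nor the hospital intercept removes the difference. The primary analysis also keeps only patients who received in-hospital antibiotics in at least one window, a condition that arises after allocation.

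Whether a patient with a label receives a first-line beta-lactam plausibly depends on which drug the label names, how severe the reaction was and how old the label is. By naming these as subgroups, the plan treats them as relevant to the primary endpoint. Yet the adjusted model contains only general health variables. What is at stake is avoidable confounding of the phase effect, and a primary result that is hard to defend if label characteristics turn out to be unbalanced.

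**Working it through.** **1. The plan's own rates.** From Sample Size Determination:
- Control: (10.5% + 5%) × 30% = 4.65%, stated as 4.6%. (Starting from the rounded 10% gives 4.5%.)
- Intervention: (38% − 5%) × 30% = 9.9%, as stated.

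The primary endpoint is defined only for antibiotic-treated patients, so the 30% factor drops out: 33% − 15.5% = 17.5 points, a marginal odds ratio of (0.33/0.67) / (0.155/0.845) = 2.69. The covariate question does not depend on the stated 80% power, and adding covariates does not change the stated sample size.

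**2. Which variables are recorded and which are in the models.**

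| Variable | Source at baseline | Named subgroup | Primary model | Adjusted model |
|---|---|---|---|---|
| Age, sex, Charlson index | recorded | no | no | yes |
| Label type | culprit drug code | yes | no | no |
| Reaction severity | derivable from reported symptoms | yes | no | no |
| Time since registration | registration date | yes | no | no |
| Antibiotics earlier in the stay | recorded | no | no | no |

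**3. Chance imbalance.** Analysable patients: 0.30 × 3285 ≈ 985, about 493 per phase. For a factor with 50% prevalence (assumed), ignoring clustering, the standard error of the difference in prevalence is √(2 × 0.25 / 493) ≈ 3.2 points. An imbalance of 5 points or more is 1.57 standard errors, with probability about 12%. Ten points is about 3.1 standard errors, so it would need a systematic shift.

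**4. Size of the bias, simple form.** Bias ≈ imbalance × difference in concordance between levels of the factor. Both inputs are assumptions, because the documents give neither.
- 0.05 × 0.10 = 0.5 points
- 0.10 × 0.30 = 3.0 points

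**5. Size of the bias, logistic form.** Assume a binary factor with 50% prevalence, an outcome odds ratio of 1.5 to 3, and an imbalance of 2 to 10 points split evenly between phases. Bias = (imbalance/2) × (gap under control + gap under intervention), where the gap is the difference in concordance between the two levels of the factor.

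| True effect | Weakest case | Strongest case | Observed odds ratio |
|---|---|---|---|
| None (15.5% in both phases) | 0.01 × (5.27 + 5.27) = 0.11 points | 0.05 × (13.56 + 13.56) = 1.36 points | 1.01 to 1.11 instead of 1.00 |
| Planned (15.5% vs 33%) | 0.01 × (5.27 + 8.92) = 0.14 points | 0.05 × (13.56 + 23.49) = 1.85 points | 2.71 to 2.98 instead of 2.69 |

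Steps 4 and 5 together span about 0.1 to 3 points. The bias can run in either direction, since the sign depends on which phase has the more favourable mix.

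**6. Against the effect.** 3.0 / 17.5 = 17% of the planned difference at the extreme, and 0.1 / 17.5 is under 1% at the other end. If the true difference were 10 points (assumed), 3.0 points would be 30% of it.

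**The case against.** A reader might infer that the primary comparison is simply unadjusted. The documents do not support that. The model contains period and hospital, every hospital delivers both conditions, and a covariate-adjusted model is prespecified. Stable differences between hospitals are largely removed.

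A reader might also infer serious selection. Nonrandomized allocation concerns which hospital follows which sequence, not which patient gets the tool. Patient Inclusion says that an automated rule finds every hospitalized patient with a label and that all who are eligible are enrolled, without individual consent. What remains is drift or chance imbalance within a hospital between short phases, plus the restriction to antibiotic-treated patients. The expected-discharge exclusion also involves some judgment in an open study. The bias range is assumed, and its top end needs an imbalance of about three standard errors.

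Two claimed benefits should not be made. In a logit mixed model, adding covariates changes the conditional odds ratio and does not in general shrink its standard error, so greater power is not shown. Nor is every recorded variable a safe covariate. Antibiotics already given in the current stay may be the same courses that are scored in the day 1 window, and adjusting for them could remove part of the outcome.

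It is fair to add that severity is collected as reported symptoms, not as a category, that the completeness of those symptoms is not stated, and that the choice of covariates is partly a matter of judgment. None of this explains why a covariate list that the article has fixed includes comorbidity and leaves out the label characteristics closest to the prescribing decision. The interaction models do not fill the gap. They are exploratory and look for effect modification; they do not provide one main estimate adjusted for all three.

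**Conclusion.** The point holds as a should-fix on the choice of covariates. The primary model has no patient-level term, the adjusted model has only three general ones, and three label variables that the plan itself regards as relevant are missing from both. Period and hospital terms do not deal with changes in patient mix within a hospital.

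The likely bias is modest: about 0.1 to 3 points on the risk-difference scale, against a planned 17.5 points. This rests on assumed imbalances of 2 to 10 points, assumed prognostic strength (odds ratio 1.5 to 3, or a gap of 10 to 30 points) and, for the logistic range, a prevalence of 50%. It would not by itself produce or erase an effect of the planned size, but it could matter if the true effect is small. The documents do not show that the phases are in fact unbalanced.

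**What to change.** Before database lock, and before any outcome is examined by phase:

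1. Add label type, reaction severity category and time since label registration as main effects to the prespecified adjusted model, beside age, sex and Charlson index, all as known at inclusion.
2. State that this model carries the primary inference, and report the model with period and hospital only beside it.
3. Include prior antibiotic use only if it is restricted to courses before inclusion that do not count in the day 1 window. If the two cannot be separated, leave it out. Add no variable measured after inclusion.
4. Report a standardized risk difference with the odds ratio, because the conditional odds ratio changes with the covariate set.
5. Fix in advance the rule that turns reported symptoms into a severity category, and the handling of records where symptoms or dates are missing.

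**Cost.** No new data items are needed, but severity has to be derived and may be incomplete. The change needs a dated amendment with its reason. The trial is open-label, more than 3000 patients are enrolled and clear-cut outcomes are scored unblinded by the central team, so a later change to the primary model could look data-driven. The detailed analysis plan is still to be finalized before lock and is the natural place for the change.
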